## Abstract

**Background:**

Several investigations are currently available to establish the diagnosis of coronary heart disease (CHD). Of these, cardiovascular magnetic resonance (CMR) offers the greatest information from a single test, allowing the assessment of myocardial function, perfusion, viability and coronary artery anatomy. However, data from large scale studies that prospectively evaluate the diagnostic accuracy of multi-parametric CMR for the detection of CHD in unselected populations are lacking, and there are few data on the performance of CMR compared with current diagnostic tests, its prognostic value and cost-effectiveness.

**Methods/design:**

This is a prospective diagnostic accuracy cohort study of 750 patients referred to a cardiologist with suspected CHD. Exercise tolerance testing (ETT) will be preformed if patients are physically able. Recruited patients will then undergo CMR and single photon emission tomography (SPECT) followed in all patients by invasive X-ray coronary angiography. The order of the CMR and SPECT tests will be randomised. The CMR study will comprise rest and adenosine stress perfusion, cine imaging, late gadolinium enhancement and whole-heart MR coronary angiography. SPECT will use a gated stress/rest protocol. The primary objective of the study is to determine the diagnostic accuracy of CMR in detecting significant coronary stenosis, as defined by X-ray coronary angiography. Secondary objectives include an assessment of the prognostic value of CMR imaging, a comparison of its diagnostic accuracy against SPECT and ETT, and an assessment of cost-effectiveness.

**Discussion:**

The CE-MARC study is a prospective, diagnostic accuracy cohort study of 750 patients assessing the performance of a multi-parametric CMR study in detecting CHD using invasive X-ray coronary angiography as the reference standard and comparing it with ETT and SPECT.

**Trial Registration:**

Current Controlled Trials ISRCTN77246133

## Background

Coronary heart disease (CHD) is a major cause of morbidity and mortality in the UK, affecting approximately 2.6 million people [1]. In a typical hospital setting, a variety of investigations may be used to diagnose CHD, risk stratify patients and plan their clinical management. The highest risk patients may proceed directly to X-ray coronary angiography, but the vast majority of patients at low to intermediate risk undergo non-invasive assessment in the form of exercise tolerance testing (ETT), stress echocardiography or single photon emission computed tomography (SPECT), in order to identify those most likely to require coronary revascularisation. The diagnostic process commonly involves a multiple-test strategy, either due to limitations in the performance of any individual test (e.g. ~30% of patients may be physically unable to perform an adequate ETT) or limitations in the test's diagnostic accuracy. For example, the reported sensitivity and specificity of ETT for angiography-proven CHD was 68% and 77% respectively from a large meta-analysis where the prevalence of CHD was high at over 60% [2]. SPECT provides greater diagnostic accuracy than ETT, 86% and 74% sensitivity and specificity respectively, compared to X-ray angiography for the diagnosis of CHD [3], being typically performed in patients with equivocal ETT results, those who cannot exercise or those who have fixed resting ECG abnormalities such as left bundle branch block [3].

The need for a reliable screening tool to select patients for invasive X-ray coronary angiography stems from the risks associated with exposure to ionising radiation and the small but significant morbidity and mortality associated with the procedure (0.11% risk of procedural death, 0.05% myocardial infarction, 0.07% stroke) [4]. The issue of radiation is often overlooked, but the risk of developing a solid tumour has been estimated at 1 in 2500 diagnostic coronary angiographic procedures [5,6]. In 2006, approximately 216,000 X-ray coronary angiograms, 74,000 percutaneous coronary interventions [7] and 20,000 coronary artery bypass graft operations were performed in the UK [8]. It is therefore evident that a significant proportion of patients undergoing coronary angiography do not subsequently require revascularisation and hence the X-ray coronary angiogram is performed only for diagnostic purposes. Cardiac Magnetic Resonance (CMR) might reliably identify those patients who actually require revascularisation and thereby reduce the need for unnecessary invasive investigation in the remainder.

### CMR imaging

CMR is the most accurate and reproducible technique for morphological imaging of the heart because of its outstanding image resolution and tissue contrast. In addition to providing detailed anatomical information, CMR can assess myocardial function, perfusion, tissue viability, coronary artery anatomy and coronary blood flow with accuracy similar or superior to that provided by other established tests (Fig. 1) [9-16]. Furthermore, CMR is safe, non-invasive and does not expose patients to ionising radiation.

**Figure 1 F1:**
[figure not shown]
**Sample cardiac MR images**. A) Standard four chamber SSFP view of the heart LV showing both atria and ventricles. B) Vertical long axis late gadolinium enhancement view of the LV showing infarction of the anteroapical wall (arrow). C) Short axis view of the LV showing a perfusion defect in the inferior wall (arrow). D) Typical MR angiogram of a right coronary artery.

A major strength of CMR is that ventricular function, tissue viability, myocardial perfusion and coronary anatomy can be assessed in a single comprehensive study [15,16]. To obtain equivalent information by current clinically validated techniques would require a combination of echocardiography, ETT and/or SPECT as well as invasive or CT coronary angiography. CMR may therefore more accurately and more cost effectively identify those patients with suspected CHD who require coronary revascularisation than the current 'battery of tests'. It has been shown that combining the four components function, viability, perfusion and coronary anatomy into a single CMR examination improves the sensitivity for the diagnosis of significant CHD over and above that for any individual component, with a combined sensitivity and specificity for the comprehensive analysis of 96% and 83% respectively [16]. These findings have been corroborated by a recent study by Klem *et al*, which found the combination of CMR perfusion and late gadolinium enhancement CMR to be superior in detecting coronary artery disease than CMR perfusion alone [17].

The recent MR-IMPACT study was the first multi-centre study comparing the diagnostic ability of CMR and of SPECT in comparison with X-ray angiography in 241 patients and showed equal performance of the two tests [18]. An important limitation of this and previous CMR publications as well as most of the SPECT literature, is that the recruited patients were already listed for coronary angiography or that analysis was retrospective, introducing an important selection bias into these studies.

### Aims and objectives

The primary objective of this study is to assess the diagnostic accuracy of CMR in detecting significant CHD compared to the current 'reference standard' X-ray angiography. Secondary objectives will be to a) compare the diagnostic accuracy of CMR in detecting significant CHD against the current standard clinical investigations of ETT and SPECT; b) assess the prognostic value of CMR in predicting time to a major adverse cardiovascular event and c) to evaluate the cost effectiveness of CMR in a diagnostic strategy for the systematic investigation of patients with suspected CHD.

## Methods

### Study design

This is a prospective, diagnostic accuracy cohort study of patients referred to cardiologists for the further evaluation of symptoms thought to be angina pectoris. All recruited patients will undergo SPECT, CMR, ETT (when physically capable) and X-ray angiography as part of this study. Patients will be recruited from Leeds Teaching Hospitals NHS Trust, Leeds, UK and Pinderfields Hospital, Wakefield, UK. All SPECT and CMR scans will be undertaken at Leeds General Infirmary. The study will be performed in accordance with the Declaration of Helsinki (October 2000), with all patients providing informed written consent. The study protocol and other relevant documentation has been approved by the Leeds (West) Research Ethics Committee (REC). Patients will then be randomised, via an automated 24-hour randomisation system, to the order in which they undergo SPECT and CMR imaging. Stratified permuted block randomisation will be used to ensure that the groups are well balanced for age (<65, ≥65) and gender. Finally all patients will undergo X-ray coronary angiography, regardless of the treating physician's chosen clinical pathway, within 4 weeks of randomisation, which will act as the reference standard.

Statistical analyses will be carried out by the Clinical Trials Research Unit (CTRU), University of Leeds, UK and the Centre for Health Economics, University of York, UK. The study population will be followed up prospectively for a minimum of 3 years to establish the prognostic value of CMR in predicting long-term major cardiovascular events.

### Eligibility

Inclusion criteria for the study are stable symptoms thought to be angina pectoris, at least one cardiovascular risk factor (smoking, family history of premature cardiovascular disease, arterial hypertension, hyperlipidaemia, diabetes mellitus), body weight less than 110 kg, suitability for coronary revascularisation if required and sinus rhythm.

Exclusion criteria for the study are previous coronary artery bypass surgery (but not percutaneous coronary intervention), evidence of crescendo angina or acute coronary syndrome, contraindication to CMR imaging (e.g. pacemaker, intra-orbital metallic debris, intracranial clips) or adenosine infusion (regular adenosine antagonist medication, reversible airways disease, second or third degree atrio-ventricular heart block, sino-atrial disease), pregnancy, known adverse reaction to Gadolinium-based contrast agents, inability to lie supine for 60 minutes and chronic renal failure (estimated glomerular filtration rate ≤ 30 ml/min).

### Recruitment and data collection

Patients will be identified from consecutive referrals to rapid access chest pain and general cardiology clinics in the Leeds and Wakefield area, which has a combined population of approximately one million people. Patients will be reviewed by a clinician and will have an ETT if they are physically able. Patients who are deemed suitable and who are proceeding for further investigations will be offered the chance to participate in the study.

An anonymised log of all patients screened for eligibility who are not recruited either because they are ineligible or because they decline participation will be kept. If a patient is enrolled in the study, information on risk factors including age, gender, cholesterol, blood pressure, smoking and diabetes, will be collected. After enrolment, the treating clinician will be asked to make a provisional diagnosis (definite angina, probable angina, possible angina or atypical symptoms) and indicate what their planned sequence of investigations (with options of ETT, SPECT and X-ray angiography or none) for this individual patient would have been, had they not participated in the study. This clinical intention record will allow assessment as to whether the use of CMR, or SPECT, impacts on the outcome for individual patients. It will not affect the study investigations and every patient will undergo all three study investigations in the order prescribed for the study.

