#### Major adverse coronary events

To assess the prognostic value of CMR, patients will be followed for three years from test completion for the occurrence of a major adverse coronary event (MACE) which will be a composite endpoint comprising at least one of the following; death from cardiovascular cause, acute coronary syndrome (with clinical and biomarker evidence), late revascularisation (>3 months after the initial coronary angiogram) and hospital admission for any cardiovascular cause.

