### Statistical considerations

#### Sample size

For our primary objective, estimating the diagnostic accuracy of CMR against the reference standard of X-ray angiography we calculated that a sample size of 750 patients would enable us to estimate the sensitivity or specificity of CMR to within +/-3.5%. This assumes a sensitivity (or specificity) of 90% for CMR and 60% prevalence of significant CHD in the study population and is based on the precision of the 95% confidence interval for a proportion. For the secondary objectives of comparing the diagnostic accuracy of CMR with SPECT and also ETT, this number would be sufficient to detect a 6.5% difference in sensitivities (or specificities) between CMR and SPECT with 80% power, assuming a sensitivity of 85% for SPECT and 2-sided analyses at the 5% significance level [22]. As the sensitivity and specificity of ETT is expected to be lower at around 68% sensitivity and 77% specificity, our sample size will provide sufficient power to detect the expected larger differences between CMR and ETT.

To assess the prognostic value of CMR in predicting MACE approximately 10 events are required for each prognostic factor in the statistical model [23]. The prognostic value of the combined CMR conclusion will be assessed after adjusting for the known risk factors age, gender, cholesterol, blood pressure, smoking and diabetes, which would require 70 events. It is estimated that approximately 30% of patients will undergo planned revascularisation based on the angiogram result and for this to be carried out usually within 8 weeks. For the remaining patients we estimate that for every 70 patients, 10 will be normal with an event rate of <1% per year and 60 will have CHD (30 significant and 30 mild) with an event rate of approximately 5% per year. The required sample size of 750 patients for the diagnostic accuracy evaluation would therefore result in approximately 23 patients experiencing an event per year. With a minimum follow-up period of 3 years this would provide the required number of 70 patients with an event.

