#### Prognostic value of CMR (at 3 year follow-up)

The prognostic ability of the combined CMR result alone and after adjusting for the risk factors: age, gender, cholesterol, blood pressure, smoking and diabetes in predicting time to the first major cardiovascular event will be assessed using Cox proportional hazards modelling. Patients not experiencing an event will be treated as censored at their last known follow-up assessment. Hazard ratios and 95% CI will be reported and Kaplan-Meier curves will be calculated. This analysis will be for all patients. Allowing physicians access to SPECT results is ethically unavoidable but may also influence revascularisation decisions and thus introduce an analysis bias. In order to account for any possible bias and any differences in the risk of future events resulting from decisions about revascularization we will conduct additional analyses which will adjust for the impact of revascularization on outcomes by treating it as an intermediate event, using time-dependent covariates and multistate models[24].

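### The adjusted Cox model omits the symptom diagnosis recorded at enrolment, so its CMR hazard ratio should not be read as prognostic value beyond clinical assessment

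*Protocol article*

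**What the plan says.** Under Recruitment and data collection, after enrolment "the treating clinician will be asked to make a provisional diagnosis (definite angina, probable angina, possible angina or atypical symptoms"). The clinician also states which tests would have been planned outside the study. The article gives this record one purpose: "This clinical intention record will allow assessment as to whether the use of CMR, or SPECT, impacts on the outcome for individual patients". It assigns the record no role as a covariate.

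Under Prognostic value of CMR, the combined CMR result is assessed alone and "after adjusting for the risk factors: age, gender, cholesterol, blood pressure, smoking and diabetes in predicting time to the first major cardiovascular event". The additional analyses there bring in only revascularisation, as an intermediate event.

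The Sample size section is built on the same list. It states that "approximately 10 events are required for each prognostic factor in the statistical model", and so "adjusting for the known risk factors age, gender, cholesterol, blood pressure, smoking and diabetes, which would require 70 events".

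The MACE composite includes "late revascularisation (>3 months after the initial coronary angiogram) and hospital admission for any cardiovascular cause". The objective, under Aims and objectives, is to "assess the prognostic value of CMR in predicting time to a major adverse cardiovascular event".

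**The concern.** The grade is the clinician's own estimate, without CMR, of how likely the symptoms are to be angina. If it carries information on CHD, it is associated with the CMR result, because CMR is planned as an accurate detector of significant CHD. It may also be associated with the endpoint. Late revascularisation and cardiovascular admission depend partly on symptoms and clinical decisions, and the X-ray Angiography section says CMR results will not routinely reach clinicians, whereas the treating clinician knows the symptom picture.

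A baseline variable linked to both the test result and the outcome, measured but left out, can make CMR look more informative than it is. Treating revascularisation as an intermediate event does not remove this, since the grade precedes it. At stake is how secondary objective (b) is read: an adjusted hazard ratio above 1 could be taken as information CMR adds to the clinic visit when part of it was already available there.

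**Working it through.** **1. The plan's own event figure.**
- Required: 10 events × (6 risk factors + CMR) = 10 × 7 = 70.
- Expected: 750 × 0.70 = 525 patients without planned revascularisation. Of these, 525 × 10/70 = 75 are normal and 525 × 60/70 = 450 have CHD.
- Events per year: 450 × 0.05 + 75 × (0 to 0.01) = 22.5 to 23.25, the stated figure of about 23. Over 3 years: 67.5 to 69.75.

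The plan's 70 reproduces, and the seven terms use all of it. Adding the grade as coefficients would break the 10-per-factor rule: one term needs 80 events and three indicator terms need 100, against about 70 expected.

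**2. Assumptions for the size of the effect.** From the document: 60% prevalence of significant CHD, and 90% sensitivity and specificity. Not from the document: half the patients are definite or probable angina, and prevalence by class is 70/50%, 75/45% or 80/40% (each averaging 60%). With this accuracy, P(CMR+ | class) = 0.1 + 0.8 × prevalence.

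**3. Case A: symptom class has its own hazard ratio h for MACE, and CMR has no true effect within class.** Let q+ and q− be the share with definite or probable angina among CMR-positive and CMR-negative patients. The spurious CMR hazard ratio is about [1 + (h − 1)q+] / [1 + (h − 1)q−].
- 70/50%, h = 1.5: q+ = 0.66/1.16 = 0.569, q− = 0.34/0.84 = 0.405; 1.284/1.202 = **1.07**.
- 75/45%, h = 2: q+ = 0.70/1.16 = 0.603, q− = 0.30/0.84 = 0.357; 1.603/1.357 = **1.18**.
- 80/40%, h = 2.5: q+ = 0.74/1.16 = 0.638, q− = 0.26/0.84 = 0.310; 1.957/1.464 = **1.34**.

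Simulation of these cases (4,000 trials each, 750 patients, about 69 events) agrees:

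| Case | HR, unstratified | Rejection at 5% | HR, stratified | Rejection at 5% | SE, unstratified to stratified |
|---|---|---|---|---|---|
| 70/50%, h = 1.5 | 1.08 | 5.3% | – | – | – |
| 75/45%, h = 2 | 1.19 | 9.4% | 1.00 | 4.6% | 0.252 to 0.259 |
| 80/40%, h = 2.5 | 1.35 | 20.5% | 1.00 | 5.1% | 0.257 to 0.269 |

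The standard error rises by 0.259/0.252 − 1 = 2.8% and 0.269/0.257 − 1 = 4.7%.

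**4. Case B: symptoms act only through disease.** Use the Sample size event rates: 1% a year if normal, 5% with mild or significant CHD. Take any-CHD prevalence as 60/70 = 86% (the plan's mix without planned revascularisation) or 90% (30 revascularised plus 60 of the remaining 70, per 100). Further assumptions: the classes differ in any-CHD by half their difference in significant CHD, and no one is removed for revascularisation. The most extreme case is 80/40% with 90% any-CHD:
- Definite/probable: 0.80 significant, 0.20 mild, 0 normal. CMR+ share 0.74, events 0.0370; CMR− share 0.26, events 0.0130.
- Possible/atypical: 0.40 significant, 0.40 mild, 0.20 normal. CMR+ share 0.42, events 0.0202; CMR− share 0.58, events 0.0218.
- Ignoring class: (0.0572/1.16)/(0.0348/0.84) = 1.190.
- Within class (Mantel-Haenszel): (0.0370 × 0.26 + 0.0202 × 0.58)/(0.0130 × 0.74 + 0.0218 × 0.42) = 0.02134/0.01878 = 1.136.
- Inflation: 1.190/1.136 = **1.05**.

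The same steps give 1.01 for 70/50% at either any-CHD figure, and 1.04 for 80/40% at 86%. If the grade is unrelated to the CMR result, or has no prognostic effect once CMR is known, the factor is 1.00.

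Neither case includes the six risk factors, which may already carry part of the association.

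**The case against.** The strongest reply is that the plan never promises what the omission would undermine. It asks for the prognostic value of CMR alone and after named risk factors, prespecifies that model identically in two places, and matches it to the event count. The aim is prediction, so the symptom grade is a competing predictor and choosing predictors is a modelling judgement. This stands in part: the planned model is not internally wrong, and the document nowhere says that its hazard ratio measures what CMR adds to the clinician's assessment.

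A reader might infer that objective (b) is biased towards CMR, or that an adjusted CMR effect would be nothing but the angina history. The document does not support that. It reports no link of the grade with CMR or MACE. The larger figures in Case A come from an assumed direct symptom effect, and under the plan's own disease-driven event rates the inflation almost vanishes.

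The grade is also not pure history. Clinic review and ETT come before the study is offered, so it may reflect the ETT result. That is still information held before study imaging, so the argument for adjustment is unaffected.

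The events objection is right for added coefficients but does not apply to stratification. Nor does the later analysis plan promised in the Analysis plan section settle the point, because the protocol itself fixes the covariate list.

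**Conclusion.** The point holds as a limit on interpretation and a reason for one supplementary analysis. The grade is recorded, is absent from a covariate list stated twice, and is not handled by any other analysis. The adjusted CMR hazard ratio can therefore include what the clinician already knew, and should not be reported as value beyond clinical assessment on the planned model alone.

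The size cannot be derived from the document. It is about 1.00 to 1.05 if symptoms act only through disease, and about 1.07 to 1.34 if a residual symptom hazard ratio of 1.5 to 2.5 exists. Both rest on an assumed even split of symptom classes and assumed prevalences by class, before adjustment for the six factors. The primary objective and the comparisons of diagnostic accuracy are untouched.

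**What to change.** In Prognostic value of CMR, keep the six-factor Cox model and prespecify beside it the same model stratified by provisional diagnosis, definite or probable against possible or atypical. Use only the record made before any study imaging result is known, and say so, since the article states only that it is made after enrolment. Add that prognostic value beyond clinical assessment will be claimed only if the CMR effect holds in the stratified model.

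The cost is a few sentences, as the variable is already collected. Stratification estimates no coefficient, so the seven terms and 70 events are unchanged. The drawbacks are a standard error about 3% wider (about 5% in the most extreme case examined), no estimate of the grade's own prognostic effect, and some residual difference within the two collapsed strata.
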